## Abstract

**CONTEXT AND OBJECTIVE::**

Major depressive disorder (MDD) is a common psychiatric condition, mostly treated with antidepressant drugs, which are limited due to refractoriness and adverse effects. We describe the study rationale and design of ELECT-TDCS (Escitalopram versus Electric Current Therapy for Treating Depression Clinical Study), which is investigating a non-pharmacological treatment known as transcranial direct current stimulation (tDCS).

**DESIGN AND SETTING::**

Phase-III, randomized, non-inferiority, triple-arm, placebo-controlled study, ongoing in São Paulo, Brazil.

**METHODS::**

ELECT-TDCS compares the efficacy of active tDCS/placebo pill, sham tDCS/escitalopram 20 mg/day and sham tDCS/placebo pill, for ten weeks, randomizing 240 patients in a 3:3:2 ratio, respectively. Our primary aim is to show that tDCS is not inferior to escitalopram with a non-inferiority margin of at least 50% of the escitalopram effect, in relation to placebo. As secondary aims, we investigate several biomarkers such as genetic polymorphisms, neurotrophin serum markers, motor cortical excitability, heart rate variability and neuroimaging.

**RESULTS::**

Proving that tDCS is similarly effective to antidepressants would have a tremendous impact on clinical psychiatry, since tDCS is virtually devoid of adverse effects. Its ease of use, portability and low price are further compelling characteristics for its use in primary and secondary healthcare. Multimodal investigation of biomarkers will also contribute towards understanding the antidepressant mechanisms of action of tDCS.

**CONCLUSION::**

Our results have the potential to introduce a novel technique to the therapeutic arsenal of treatments for depression.

## INTRODUCTION

Major depressive disorder (MDD) is a psychiatric condition with high prevalence and recurrence worldwide,^1^ and it is projected to be the second greatest cause of disability worldwide in 2020.^2^ However, antidepressant drugs are only moderately effective for MDD treatment.^3^ Moreover, common adverse effects can lead to treatment discontinuation and recrudescence of symptoms.^4^ For these reasons, novel treatment strategies are continuously pursued.

In this context, non-invasive brain stimulation therapies (electroceuticals) have been increasingly investigated as non-pharmacological MDD treatments, such as repetitive transcranial magnetic stimulation (rTMS), a technique that discharges potent electromagnetic fields through a coil placed over the patient’s head.^5^ Repetitive TMS is an effective treatment for MDD,^6^^,^^7^ although issues such as high cost of application, discomfort and specialized technology limit widespread adoption.^8^

Transcranial direct current stimulation (tDCS) is a neuromodulatory technique that presents low cost, high portability and a benign profile of adverse effects and is relatively simple to use.^9^^,^^10^ It consists of applying a low-intensity electric current across the patient’s head using two electrodes on the scalp. In a seminal study in 2000, Nitsche and Paulus demonstrated that anodal and cathodal tDCS applied over the motor cortex respectively increased and decreased motor cortical excitability, as measured by means of TMS motor-evoked potentials,^11^ thereby showing that tDCS could alter cortical excitability.^12^ Its effects depend not only on the polarity of the current, but also on other factors, such as baseline cortical activity, neuronal orientation and delivered current intensity and duration.^13^^,^^14^^,^^15^

The use of tDCS for MDD is based on findings from neuroimaging studies (such as Mayberg et al.^16^), which suggest that the depressive state is associated with hypoactivity of prefrontal areas, particularly the left dorsolateral prefrontal cortex (DLPFC), and that it can be resolved through an increase in the activity of this area. Therefore, treatment strategies that increase left DLPFC activity might treat depressive symptoms. This approach has been adopted and validated in studies using high-frequency (excitatory) rTMS^6^ and anodal tDCS over the DLPFC.^17^ Alternatively, some trials have applied the cathode over the right DLPFC (such as Ferrucci et al.^18^), or have used low-frequency (inhibitory) rTMS over this region,^19^ in accordance with the prefrontal asymmetry theory of depression that states that the right DLPFC presents abnormally high activity during depressive episodes.^20^

Several non-controlled and controlled studies using tDCS for MDD have been published, from 2006 onwards.^17^ In the first randomized clinical trial (RCT) in this field, Fregni et al.^21^ showed the efficacy of active tDCS versus sham for ameliorating depressive symptoms, in a pilot study on 10 patients. More recent RCTs enrolling larger samples^22^^,^^23^ have shown that active tDCS was an effective treatment for MDD. Its efficacy was corroborated by a recent meta-analysis.^24^ However, exhaustive RCTs addressing tDCS efficacy are still needed, since some results from RCTs have been non-significant,^25^^,^^26^^,^^27^ the total number of subjects investigated is still low and the optimal parameter protocols for tDCS in MDD remain to be determined.

In a recent factorial, placebo-controlled trial named SELECT-TDCS (Sertraline versus Electric Current Therapy for Treating Depression Clinical Study), we assessed the efficacy of tDCS combined and compared with sertraline 50 mg/day for treating 120 depressed patients.^28^ After two weeks of treatment and at the endpoint, the combined treatment was statistically superior to the other groups in terms of depression improvement and response and remission rates. Transcranial DCS was also superior to the other groups at the endpoint and not statistically different from sertraline^23^ (Figure 1). The main findings from this study were the synergistic effects of the combination of tDCS and sertraline and the efficacy of tDCS as monotherapy. However, although sertraline and tDCS efficacy did not statistically differ, we could not extend these results to claim similar efficacy for tDCS and antidepressant pharmacotherapy, because of study limitations such as the low dose of sertraline used, the relatively short trial duration, the finding that the sertraline group was not superior to placebo and the relatively underpowered comparison of tDCS versus sertraline.

**Figure 1. f1:**
[figure not shown]
Main results of the SELECT-TDCS trial. The figure shows the primary outcome of the Sertraline versus Electric Current Therapy for Treating Depression Clinical Study (SELECT-TDCS).^23^ The x-axis represents depression scores measured using the Montgomery-Asberg depression rating scale (MADRS). The y-axis shows changes in depression scores over time according to the treatment group. Adapted from Brunoni et al.^23^

## OBJECTIVE

Therefore, whereas we showed in SELECT-TDCS that tDCS combined with pharmacotherapy could enhance improvement of depression, the main study aim of ELECT-TDCS (Escitalopram versus Electric Current Therapy for Treating Depression Clinical Study) is to compare the efficacy of tDCS with a fully dosed, first-line antidepressant treatment (escitalopram 20 mg/day).

In this paper, we describe the rationale, design and methodology of the ongoing ELECT-TDCS trial. The trial started in October 2013 and plans to enroll 240 patients by January 2017. As of November 2014, approximately 130 patients had already been recruited.

## METHODS

### Overview

The ELECT-TDCS trial randomizes patients into: sham-tDCS/placebo-pill (placebo group), sham-tDCS/escitalopram (escitalopram group) and active-tDCS/placebo-pill (tDCS group). It was approved by the Local and National Ethics Committee (CAAE:10173712.3.0000.0076) of the University Hospital and Clinics Hospital of the University of São Paulo and is registered in clinicaltrials.gov (NCT01894815). All study participants provide written, informed consent for participation in the study.

Our null hypothesis is that the improvement, i.e. the difference in efficacy between baseline and endpoint measurements of the tDCS group (µ_tDCS_) will be less than or equal to 50% (retention fraction *f* ≤ 50%) of the difference in the improvement between escitalopram and placebo (µ_drug_ - µ_placebo_). The study’s primary aim is to prove the alternative hypothesis, i.e. that this difference is greater than 50% (*f* > 50%).

$$H_{o}:\;{µ}_{tDCS}\;-\;{µ}_{placebo}\;\leq \;50\%\;({µ}_{drug}\;-\;{µ}_{placebo})$$

*or*

$$H_{o}:\;{µ}_{tDCS}\;-\;0.5\;{µ}_{placebo}\;-\;0.5\;{µ}_{drug}\;\leq \;0$$

$$H_{A}:\;{µ}_{tDCS}\;-\;{µ}_{placebo}>\;50\%\;({µ}_{drug}\;-\;{µ}_{placebo})$$

*or*

$$H_{A}:\;{µ}_{tDCS}\;-\;0.5\;{µ}_{placebo}\;-\;0.5\;{µ}_{drug}>\;0$$

In a non-inferiority triple-arm trial, there are three relevant comparisons: (1) experimental treatment versus active comparator (i.e. tDCS versus escitalopram); (2) experimental treatment versus placebo; and (3) active comparator versus placebo. Authors such as Koch and Röhmel^29^ have considered that the third comparison is not strictly necessary if the former two were significant, but in their approach, two or three null hypotheses would have to be independently rejected (thereby decreasing the P value), or the trial would only be valid if all hypotheses were rejected.^30^ Therefore, we use here an alternative model presented by Pigeot et al.^31^ and already used in the literature,^32^ in which the study aim can be presented in a single H_0_, which simultaneously tests the non-inferiority between active treatments and their superiority against placebo, thereby decreasing the number of multiple comparisons.

Our secondary aims are to explore the clinical improvement in terms of response status (more than 50% of improvement from baseline to endpoint) and remission status (HDRS-17 ≤ 7 at endpoint). We will also explore improvement in depression using the MADRS and the BDI. Finally, we will also investigate whether any early improvement (week 3) was observed between the groups.

We also aim to identify several predictors and mediators of tDCS response, as described below.

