### Design and sample size determination

ELECT-TDCS uses a non-inferiority, triple-arm, placebo-controlled design, with 3:3:2 permuted block randomization in which participants are respectively assigned to escitalopram, tDCS or placebo. Our aim is to prove that tDCS is non-inferior (i.e. that it has similar or superior efficacy) to escitalopram. The placebo group is used for the following purposes. (1) To ensure assay sensitivity. The placebo ascertains that a similar result between escitalopram and tDCS occurred not due to a false-positive finding caused by methodological issues such as insufficient sample size, sample bias, poor blinding, etc., but in fact due to true equivalence between treatments. (2) To allow direct (superiority) comparisons between the pharmacological treatment and placebo, which is critical, since up to 50% of antidepressant drug trials fail to detect superiority between the active treatment and placebo.^78^ (3) To allow direct comparisons between the experimental treatment and placebo, given that evidence of tDCS efficacy is still being established. (4) To avoid setting up an arbitrary efficacy margin, which would be a problematic approach because the active comparator in the trial will not necessarily have the same efficacy as previous findings in the literature.^79^ For these reasons, the non-inferiority design with a placebo group is considered to be the gold standard for this type of trial according to the US Food and Drug Administration (FDA) and the European Medical Agency (EMA).^80^

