The M_2_ margin (relative efficacy of the experimental treatment to the active comparator) is based on a fraction retention factor (*f)* of the M_1_, given that the relative efficacy of the experimental treatment to the active comparator could only be larger than the efficacy with placebo if the active comparator is worse than placebo. The fraction retention varies according to the condition investigated: for instance, in studies focusing on vaccines and oncology, the *f* value should be close to 1; whereas for chronic and functional disorders, this value ranges between one-half and one-third.^31^^,^^79^ There is no consensus regarding the *f* value in non-inferiority trials for MDD, although Nutt et al.^81^ proposed that for generalized anxiety disorder, the value should be 50%. In this trial, we adopted the *f* value of 50%, based on Nutt et al.^81^ and considering that MDD is comparable to generalized anxiety disorder with regard to methodological aspects (large placebo response, short duration of clinical trials, similar pharmacological treatments, comparable scales etc.).

Therefore, in our trial, M_2_/M_1_ = 0.5, although M_1_ is based on the difference between the active comparator and placebo and it will be known only when the study has been finished. Although this approach indexes the relative efficacy of tDCS versus escitalopram according to the placebo response of the study, it is theoretically possible that the escitalopram-placebo difference is too large, thus producing a large M_2_ value that could favor a finding that comparison between escitalopram and tDCS does not show any significant difference, even if escitalopram clinically outperforms tDCS. To avoid this issue, we will only consider that tDCS was non-inferior to escitalopram if the mean difference between escitalopram and tDCS is less than 3 points on the HDRS-17. The threshold of 3 points was chosen considering the National Institute for Health and Clinical Excellence (NICE) guidelines, which establish that this is a clinically meaningful difference in efficacy.^82^

To determine the sample size, we first needed to establish the randomization proportions between the groups. Pigeot et al.^31^ recommended a 1:1:k_p_ ratio, where k_p_ is determined according to the fraction retention factor, as shown below:

$$k_{placebo}\;=\;\left[(1\;-\;f)\;\surd 2\;+\;2f\right]/(1\;+\;f^{2})$$

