According to this formula, for *f* = 0.5, k_p_ is 0.69. Therefore the optimal proportion for allocation between the groups is 1:1:0.69, or approximately 3:3:2, as used in ELECT-TDCS.

We estimated our sample size in accordance with the suggestion of Pigeot et al.^31^ for non-inferiority, triple-arm trials:

$$N_{arm}\geq {\left(t_{1-\alpha ,\;3n-3}\;+\;t_{1-\beta ,\;3n-3}\right)}^{2}*(1+f^{2}+{\left(1-f\right)}^{2})\;{*\left[\left(\sigma /\;{µ}_{DRUG}-{µ}_{PLACEBO})/(r-f\right)\right]}^{2*}$$

This formula shows that the sample size is a product of three factors (in parentheses). The factor in the first parentheses take into account the values of α and β, which were, respectively 0.025 (one-tailed) and 0.2. The factor in the second parentheses is the *f* value (the higher the *f* value is, the larger the necessary sample size will be), which was determined as 0.5 for our study. The factor in the last parentheses involves the standard deviation and effect sizes of the interventions. We took the value of the standard deviation to be a function of the difference in efficacy between the active comparator and the placebo:^31^

$$\sigma =\varepsilon \;({µ}_{DRUG}-{µ}_{PLACEBO})$$

The ε value indicates that the standard deviation is associated with the mean difference values observed in the study. It ranges from 0.2 to 2, and values > 1 are considered conservative. In the present study, we took the ε value to be 1.5, i.e. the standard deviation would be 1.5 times the value of the difference in efficacy between the active intervention and the placebo, which is compatible with depression studies in which the variance is usually high.^†^

Therefore, considering an attrition rate of 13% (similar to SELECT-TDCS), β = 0.2, α_one-tailed_ = 0.025, *f* = 0.5 and ε = 1.5, a total sample of 240 patients will be necessary in order to reject our null hypothesis. For 3:3:2 randomization, this means that in the end, 90, 90 and 60 patients will be respectively allocated to the tDCS, escitalopram and placebo groups.

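### Rejecting the single null hypothesis does not test superiority over placebo, so retention of half of escitalopram's effect can be declared when the trial has shown no escitalopram effect

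*Protocol article*

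**What the plan says.** The Overview writes the alternative hypothesis as mean improvement on tDCS, minus half that on placebo, minus half that on escitalopram, greater than zero. It notes that "In a non-inferiority triple-arm trial, there are three relevant comparisons": tDCS with escitalopram, tDCS with placebo, and escitalopram with placebo. It sets aside an approach in which "two or three null hypotheses would have to be independently rejected (thereby decreasing the P value", and mentions separately a rule that the trial is valid only if every hypothesis is rejected. It adopts instead a single null hypothesis that, it says, "simultaneously tests the non-inferiority between active treatments and their superiority against placebo, thereby decreasing the number of multiple comparisons".

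The Statistical analysis section decides the primary hypothesis on one T statistic against a critical value of 1.97 on 237 degrees of freedom, and calls the analyses of group differences over time exploratory.

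Design and sample size determination adds one condition to the claim: the escitalopram-tDCS mean difference must be below 3 HDRS-17 points. The reason given is that "it is theoretically possible that the escitalopram-placebo difference is too large". The same section says the placebo arm is there for assay sensitivity and for direct comparisons with placebo, and warns that "up to 50% of antidepressant drug trials fail to detect superiority between the active treatment and placebo". It does not say what follows for the non-inferiority claim if those comparisons fail.

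**The concern.** The decision rule protects against an escitalopram effect that is too large and not against one that is absent. A statement that tDCS retains more than half of escitalopram's effect has content only if the trial has shown such an effect. The Introduction applies this reasoning to the investigators' earlier sertraline trial: among the reasons why similar efficacy could not be claimed, it lists that sertraline was not superior to placebo. Under the present rule the same result for escitalopram would not block the headline claim. Because the Overview says superiority is already covered by the single test, a reader would take a rejection as evidence on all three comparisons.

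**Working it through.** **Inputs.** From Design and sample size determination: retention fraction f, "which was determined as 0.5 for our study"; alpha and beta, "which were, respectively 0.025 (one-tailed) and 0.2"; and an effect assumption under which "the standard deviation would be 1.5 times the value of the difference in efficacy between the active intervention and the placebo", that is, escitalopram over placebo = 1/1.5 = 0.667 SD. Allocation is 90 tDCS, 90 escitalopram, 60 placebo. The HDRS-17 SD in points is not stated; 6, 8 and 10 are assumptions.

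**The plan's own figures.** The multiplier in T is 1/√(1/90 + 0.25/90 + 0.25/60) = 1/0.1344 = 7.44, as stated. The critical value t(0.975; 237) = 1.970, as stated. Power at the planning values, with both active arms 0.667 SD over placebo: noncentrality 7.442 × (0.667 − 0.333) = 2.48, power 69.5%. That is below the planned 80%. The sample size is a separate matter; it is noted here only because 69.5% is the baseline for costing the fix.

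**What rejection establishes.** Write D for escitalopram minus placebo and X for tDCS minus placebo, both in improvement. The alternative is X > 0.5 D.

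- D is not constrained, so escitalopram over placebo is not tested.
- X > 0 follows only if D ≥ 0.
- With D = −4 and X = −1, the alternative is true (−1 > −2) although both treatments are worse than placebo.

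**At the level of observed means.** Suppose the escitalopram and placebo means come out equal. The null is rejected once tDCS leads by 1.970/7.442 = 0.265 SD. A direct tDCS-placebo test needs 1.970 × √(1/90 + 1/60) = 1.970 × 0.1667 = 0.328 SD. A lead between the two gives a non-inferiority claim with neither active arm significantly better than placebo.

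**How often.** Take escitalopram truly equal to placebo and tDCS truly 3 points better. The noncentrality of T is 7.442 × 3/SD. The joint figures come from 400,000 simulated trials per scenario with pooled variance, 237 df and the 3-point limit applied; repeat runs differ by about 0.1 point.

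| Assumed SD | Noncentrality | Claim made | Claim made, escitalopram not significant vs placebo | Claim made, tDCS not significant vs placebo |
|---|---|---|---|---|
| 6 | 3.72 | 96% | 94% | 11% |
| 8 | 2.79 | 79% | 77% | 20% |
| 10 | 2.23 | 60% | 59% | 19% |

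The 3-point limit does not alter these rates, since an escitalopram arm with no effect meets it easily.

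**Where the gap does little.** With all three arms equal, the claim rate is 2.5%. At the planning values, escitalopram versus placebo has noncentrality 0.667/0.1667 = 4.0 and power 98%; only about 1.2% of trials make the claim with escitalopram not significant.

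**The case against.** The strongest reply concerns what the percentages mean. A reader might infer that 94%, 77% and 59% are false-positive rates. They are not: in those scenarios tDCS truly is 3 points better than both escitalopram and placebo, so the bare statement that it is no worse than escitalopram is true. What lacks support is the retention claim. A false reading that tDCS beats placebo needs escitalopram to be truly worse than placebo, which is less likely. With escitalopram 4 points and tDCS 1 point worse than placebo, the claim is made in about 23%, 15% or 11% of trials at SD 6, 8 or 10. This reply stands, and it limits the point to assay sensitivity and to the wording.

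Second, the Overview presents the need for the escitalopram-placebo comparison as debated, and cites a view that it can be dropped if the other two comparisons are significant. But that view requires a significant tDCS-placebo test, which the plan's rule does not require either.

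Third, the placebo comparisons are planned and a failed comparator would be visible; an analysis plan not shown might order the tests. That is fair as to detail. It does not rescue a stated property of the test that is wrong, or a published claim rule that does not depend on those comparisons.

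Fourth, a reader might infer that the plan's multiplicity reasoning is wrong for a rule under which all hypotheses must be rejected. The text does not support that: it ties the alpha penalty to independent rejection and lists the all-must-reject rule separately.

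Finally, a gate has a real price when escitalopram's effect is modest; the cost is set out with the fix.

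**Conclusion.** The point holds as a misstatement of what the primary test shows and as a missing condition on the claim. The algebra depends on no assumed value: rejection never tests escitalopram against placebo, and it supports tDCS over placebo only if escitalopram is at least as good as placebo. The size depends on the true escitalopram effect. At the planning values about 1 trial in 100 is affected. If escitalopram does no better than placebo and tDCS is 3 points better, most trials are affected, with the exact share resting on an assumed SD of 6 to 10 points. The document itself treats failure of the comparator as a real prospect. The type I error of the retention test is not in question.

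**What to change.** Correct the Overview sentence to say that the retention test shows only that tDCS minus placebo exceeds half of escitalopram minus placebo. Before unblinding, make the primary analysis a fixed sequence, each step at one-sided 0.025 with no alpha split:

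1. Escitalopram better than placebo on HDRS-17 improvement at week 10.
2. Only if step 1 rejects: the retention T test together with the existing 3-point limit.

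Passing both steps implies tDCS over placebo, since X > 0.5 D and D > 0. If step 1 fails, make no retention or non-inferiority claim, and report tDCS versus placebo and tDCS versus escitalopram as separately labelled results.

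The cost is power for the claim:

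- At the planning values with 90/90/60: 69.4% to 68.2%.
- With 13% attrition (78/78/52): about 63% to 61%.
- With both active arms at 0.5 SD over placebo: about 46% to 40%.
- With escitalopram at 0.333 SD and tDCS at 0.5 SD: about 70% to 37%.

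In the last case both treatments truly beat placebo and the gate often withholds a true claim. The investigators should accept that openly as the price of requiring assay sensitivity.
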